### Primary outcome measures

The primary outcome measures include the severity of BPD and severe parasuicidal behavior. 331 The BPDSI (Borderline Personality Disorder Severity Index-Leibniz Institute for Psychology) (64) is a semi structured clinical interview measure that captures specific BPS symptoms over the past three months. It contains 70 items, which are similar to the DSM-IV criteria. It covers nine areas of symptoms: *(1) abandonment; (2) interpersonal relationships; (3) identity; (4) impulsivity; (5) parasuicidal behavior; (6) affective instability; (7) emptiness; (8) outbursts of anger; and (9) dissociation and paranoid thoughts* (64). For its reliability, the internal consistency is greater than alpha = .90 (total score) or between alpha = .49 and.89 (subscales) (65). It is a reliable and valid instrument that is suitable for use as an outcome measure (64, 66). In our sector’s validation procedure of the BPDsi (67, 68), the statistical analyses revealed a fairly valid and reliable tool (Cronbach’s α = .99). A cutoff score of 15 between patients and controls has been established; thus, a score below 15, which is rated two years after randomization or earlier and maintained until follow-up, is used as a criterion for recovery (64).

**Suicide and Self-Harm Inventory** (69): The purpose of the interview is to collect accurate data about attempted suicides and self-harm incidents over a six-month period without attempting to measure their severity. Bateman and Fonagy (70, 71) define parasuicidal behavior as including three types of behavior: *1) suicide attempts (which must be intentional, life-threatening, and require medical intervention); 2) life-threatening self-harm behaviors (which must be intentional, cause visible tissue damage, and require nursing or medical intervention); and 3) admissions to a psychiatric hospital*. The Greek version will be used here (72).

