**Method and design:**

A quasi-experimental clinical trial will be conducted. The study is designed to include 212 BPD patients who will be non-randomly assigned to specialized health care services and to two TAU centers. Patients will be recruited at each site following the routine clinical pathways of referral at each center. The primary outcome measures are BPD severity, suicide attempts and hospital admissions. The secondary outcome measures will include measures of general psychopathology, psychosocial functioning, quality of life and retention in treatment. In addition. An economic evaluation from a societal perspective will be conducted.

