## Background

Borderline personality disorder (BPD) is a common mental disorder characterized by pervasive and persistent instability in interpersonal relationships, identity and affect, and marked impulsivity (1). BPD patients present high rates of comorbid mood, anxiety, substance use, eating, and other personality disorders (2, 3). BPD patients’ quality of life (QOL) is severely impaired across mental and physical dimensions (4, 5), and their social functioning is consistently poor (6). In addition, BPD patients often experience significant emotional crises, engage in self-harm injury, and make suicide threats or attempts (7, 8), resulting in extensive use of treatment services (emergency departments or inpatient hospitals) (9–12). People with BPD commit suicide at a rate of 10% (13). The point prevalence of BPD is estimated to be 1% in community settings (14).

Reports range from 0.7% to 2.7% for lifetime prevalence (15); however, a previous study in a nonclinical sample (16) reported a higher lifetime prevalence of 5.9%. In clinical settings, BPD is one of the most common PDs, with a point prevalence of approximately 12% in outpatients and 22% in inpatient psychiatric populations (14). Furthermore, 6.4% of patients in primary care settings have a BPD diagnosis (10). Epidemiological studies tend to define BPD as a categorical entity. However, compelling evidence suggests that we should understand BPD as a dimensional construct rather than a categorical one (14, 17). Even low levels of BPD symptoms, not only full-blown BPD, are associated with psychiatric comorbidities and functional disability (17).

Previous research has highlighted the increased economic burden of BPD on society due to the extensive use of health services, loss of productivity (11, 18, 19), and intersectoral costs (20). The economic burden of personality disorders, including BPD, appears to be greater than that of depression and generalized anxiety disorder and comparable to that of schizophrenia (11).

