**Figure 1 f1:**
[figure not shown]
Flowchart of the study design.

Primary outcomes will be (i) the severity of BPD symptoms and (ii) the severity of self-harm and suicidality. Secondary outcomes will be: (i) psychopathological symptom severity, (ii) quality of life, (iii) quality and intensity of interpersonal relations, (iv) functioning and (v) disability.

Mediator variables will be: (i) reflective functioning, (ii) defense style and (iii) personality organization. In other words, better primary and secondary outcomes for the intervention group as opposed to TAU group are expected to be discerned due to differences in reflective functioning, defense style and personality organization. As the design does not include random allocation of participants in the two arms, baseline measurements of the outcome variables will be considered as confounders for the ensuing measurements. Moreover, the two groups will be compared in terms of the following variables: sex, family status, education status, number of children, profession, living arrangement, physical illness, medication for BPD and prior hospitalize physical illness, medication for BPD and prior hospitalization. Those variables with a statistically significant difference between the two groups, will be considered confounder variables in the design and will be taken into consideration as such in ensuing evaluation points. Moreover, information about the treatment delivered in the two groups will be recorded; namely, duration of treatment, type and number of sessions attended. These will be included as confounder variables in the design.

The Ethics Committees of Eginition Hospital, Medical School of the National and Kapodistrian University of Athens (No. 404/05-07-2021), Attikon Hospital (No. 443 25/08/2021), and Sismanogleion General Hospital (27703/10-12-2021) approved the research protocol. The Clinical Trials.gov website has registered the trial under the ID NCT06392139 (Protocol ID No. 404/06-07-202).

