**The Work and Social Adjustment Scale** (**WSAS)** (84). It is a self-report instrument that consists of 5 items that are scored on a scale ranging from 0 to 8. We assessed functional impairment in the domains of *work, household, social leisure, private leisure, and family and relationships at the time of assessment.* The reliability, validity and sensitivity to change of the WSAS have been firmly established in samples of patients with different clinical disorders (85, 86).

The World Health Organization Disability Assessment Schedule (WHODAS 2.0) (12, 87) is a standardized assessment tool developed by the World Health Organization that assesses disability-related health conditions in the past 30 days. The measure assesses disability across six domains: cognition, mobility, self-care, getting along with others, life activities, and participation. A profile of functioning is derived across the six domains, as is a general disability score. The WHODAS 2.0 has demonstrated excellent reliability and validity (12). Across the study samples, Cronbach’s α for the overall score of global functional disability was.97, with the domain scale scores ranging from.83 (self-care) to.94 (life activities).

**Treatment Retention:** Dropouts will be recorded. An assistant researcher will contact through telephone any patient who will drop out, and if she/he agrees, an interview will be conducted to elicit the patient’ s perspective about the intervention and the reasons for dropping out. The interviews were semi structured and were developed by the research group of the study.

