#### Dropout rates

Dropout rates will be compared at the end of the study with the non-parametric criterion Mann Whitney (IV: group assignment and DV: number of drop outs), as number of drop-outs is an ordinal variable.

The Statistical Package for the Social Sciences (SPSS) version 25 (95) will be used for the statistical analyses. All significance tests will be two-tailed, with a 5% significance level and 95% confidence interval.

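### The self-harm and suicidality primary outcome does not name death by suicide and gives no source for it, so the comparison is made among survivors

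*Protocol article*

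**What the plan says.** The Design section makes self-harm and suicidality the second of two primary outcomes. The abstract words the set differently: "The primary outcome measures are BPD severity, suicide attempts and hospital admissions". Neither list contains death by suicide.

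Primary outcome measures names the instrument, the Suicide and Self-Harm Inventory, an interview whose purpose is to "collect accurate data about attempted suicides and self-harm incidents over a six-month period". It then gives three qualifying behaviours. The first is "suicide attempts (which must be intentional, life-threatening, and require medical intervention"); the others are life-threatening self-harm that needs care, and psychiatric admission. The other primary measure, the BPDSI, is also an interview.

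The Background puts suicide in this disorder at 10%, without a period. The Design section follows primary outcomes for two years and then three more, with visits every six months.

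Evaluation of effect plans a linear regression at each visit and, at the end, a repeated measures ANOVA over 11 time points. Loss appears only as dropout. Under Treatment Retention, "An assistant researcher will contact through telephone any patient who will drop out", and the Dropout rates section adds that "Dropout rates will be compared at the end of the study". Neither mentions death.

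**The concern.** A fatal suicidal act is the most serious event that a suicidality outcome can record, and by the document's own figure it is foreseeable in this population. As the outcome is defined, it has no place. The patient cannot give the next interview, so the window in which the death occurred has no value, and any non-fatal attempt earlier in that window is lost with it. Later visits compare survivors only. A standard repeated measures ANOVA, which needs every time point, would also discard that patient's earlier visits.

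At stake is whether a claim of lower suicidality can be trusted. If deaths are unevenly spread between the arms, the arm with more of them has its event rate understated, and nothing in the planned outcome would reveal it.

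**Working it through.** **Inputs from the document.** 106 patients per group, d = 0.45, power 0.90, two-sided 5% (Sample size; Statistical analyses). The sample size holds up. The normal approximation gives 104 per arm and the t-test 104.7, so 105. At 106 per arm the power is 0.903. I use n = 106 below.

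**Assumed inputs.** The document gives no suicide rate per period and no event rate. Five-year suicide rates of 2%, 5% and 10% would mean 212 × 0.02 = 4.2, 212 × 0.05 = 10.6 and 212 × 0.10 = 21.2 deaths in the trial. The last treats the undated 10% as a five-year risk and is an upper bracket. For illustration I take 3 suicides in one arm.

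**Effect on an event rate.** Let e be the patients with an event, including those who die, d the suicides and n = 106. Counting the deaths gives e/n. Leaving them out gives (e − d)/(n − d). With d = 3:

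| Assumed rate | Deaths counted | Deaths left out | Shift |
|---|---|---|---|
| about 20% | 21/106 = 19.8% | 18/103 = 17.5% | 2.3 points |
| about 30% | 32/106 = 30.2% | 29/103 = 28.2% | 2.0 points |
| about 50% | 53/106 = 50.0% | 50/103 = 48.5% | 1.5 points |

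**Scale.** The standard error of a difference between two arms of 106 is √(2p(1 − p)/106), which is 5.5, 6.3 and 6.9 points at p = 0.20, 0.30 and 0.50. Each shift is less than half of one standard error.

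**Can the direction reverse?** Only if the true difference is smaller than the net shift. Example: arm A has 21/106 events including 3 suicides (19.8%), and arm B has 20/106 with none (18.9%). Arm A is worse by 0.9 points. As written, arm A shows 18/103 = 17.5% and appears better by 1.4 points. If both arms lose 3, the shifts nearly cancel: at 20% and 30% the net change is 2.3 − 2.0 = 0.3 points.

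**Effect on a score such as the BPDSI.** If those who die would have scored k SD worse than the arm mean, the survivors' mean moves by k × d/(n − d). For d = 3 this is 0 at k = 0, 3/103 = 0.03 SD at k = 1, and 6/103 = 0.06 SD at k = 2. The last two are 6% and 13% of the planned 0.45.

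**The case against.** Four objections carry weight.

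- **This is a condensed article.** Rules for deaths and missing values usually sit in the full protocol or analysis plan, and Limitations and challenges says that statistical consultation is still to come. That covers analysis rules. It does not cover the outcome definition, which the article states and which does not name the fatal event; nor can an analysis plan use deaths that were never ascertained.
- **The definition does not expressly exclude a fatal attempt.** This is correct. The three types come from cited work and the inventory itself is not reproduced, so its scoring of a death, or its use of informants, cannot be seen. But the first type requires medical intervention, which a death before help arrives may not meet, and the article names no source beyond the interview.
- **A reader might infer that a death becomes a dropout.** No section says so. The planned telephone contact and interview about reasons for leaving describe living patients. Deaths are simply not classified. If they were counted as dropout, they would worsen that arm's retention.
- **A reader might infer that non-fatal events are rare, so that a few deaths would dominate.** The document does not support this. The Background describes frequent crises and self-harm and heavy use of emergency and inpatient care, and admissions count as events.

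In addition, the primary aim is a two-year comparison, so five-year death counts overstate the exposure for the main analysis.

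**Conclusion.** The point holds at moderate severity. A primary outcome called suicidality does not name death by suicide, gives no source for it, and as written is compared among survivors. The size depends on an unknown number of deaths. Under the assumption of 3 suicides in one arm and none in the other, that arm's event rate is understated by about 1.5 to 2.3 points.

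Two stronger conclusions are tempting and not supported. The first is that a small imbalance in deaths would turn the result around: it could reverse only a true difference below that shift, which is well inside sampling error at this sample size. The second is that an arm with more suicides would look better on the BPDSI at every later visit. That needs those who die to have been worse than average; otherwise the shift is zero. Values from visits before the death also remain in the regressions at those visits.

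**What to change.** - **Primary outcome measures:** state that death by suicide counts as an event in the six-month window in which it occurs, taken from the treating clinic's records or next of kin when the patient cannot be interviewed.
- **Reporting:** give suicides and all deaths by arm as a separate line.
- **Treatment Retention and Dropout rates:** keep deaths separate from dropout.
- **Sensitivity analysis:** use a binary outcome of any event including suicide. Assigning a worst value would not work for the incident count, because the inventory does not grade severity and no maximum is defined.

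The cost is a few sentences and a vital-status check for patients who miss a visit, which can build on the telephone contact already planned. Cause of death will be uncertain in some cases. The change is best made during follow-up, since deaths are harder to ascertain years later.

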Moreover, a longer-term evaluation will take place for both groups but only for the primary outcome variables, as the interview entailing both primary and secondary outcomes is long and by extending the evaluation time frame, we would not want to lose participants at longer follow-ups and risk the emergence of attrition bias.

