We designed this study to evaluate the effectiveness and economic aspects (cost-effectiveness and cost-utility) of the STP-BPD in everyday clinical practice, adhering to the call for *‘real-world’* clinical trials (55, 56). Therefore, we will use minimal exclusion criteria without altering clinical decision-making, health care, or treatment. Patients will be followed for 2 years for primary and secondary outcomes, and for additional 3 years for primary outcomes only. Assessment of the clinical and psychosocial outcome variables will be performed at baseline (T_0_), prior to patient allocation, and every 6 months until the end of the 2^nd^ year of follow-up (T_1_, T_2_, T_3_, and τ_4_). At baseline (T0) and then every year thereafter (τ2 and τ4), the mediators that affect the link between the type of health care service and the major clinical and psychosocial outcomes will be examined. For long-term evaluation, primary outcome variables will also be assessed at T_5_ (2 years and 6 months), T_6_ (3 years), T_7_ (3 years and 6 months), T_8_ (4 years), T_9_ (4 years and 6 months) and T_10_ (5 years). Patient flow, screening and assessments are displayed schematically in **Figure 1**.

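### The six-month look-back for suicide attempts, self-harm and admissions equals the visit interval, so if applied literally a missed or late visit leaves part of a primary outcome unasked, and the described dropout call does not cover events

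*Protocol article*

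**What the plan says.** Under Primary outcome measures, the Protocol article describes the Suicide and Self-Harm Inventory as an interview to "collect accurate data about attempted suicides and self-harm incidents over a six-month period". The definition given there has three event types: suicide attempts, life-threatening self-harm and "admissions to a psychiatric hospital".

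Under Design, outcomes are assessed at baseline, "prior to patient allocation, and every 6 months until the end of the" second year (T1 to T4). The section continues: "For long-term evaluation, primary outcome variables will also be assessed at" T5 to T10, again at half-year steps up to five years. Table 1 lists the inventory at all eleven time points.

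Under Secondary outcome measures, the Treatment Retention paragraph says that patients who drop out will be telephoned and, if they agree, interviewed on their "perspective about the intervention and the reasons for dropping out". Events are not mentioned.

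Aims and hypotheses shows that loss over time was foreseen. Long-term follow-up is limited to the primary outcomes because "we would not want to lose participants at longer follow-ups and risk the emergence of attrition bias".

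**The concern.** Attempts, life-threatening self-harm and admissions are events with dates. A patient can report them at a later interview, so an event missed because nobody asked is an avoidable loss. With a look-back equal to the visit spacing there is no slack: any departure from the timetable leaves time that no interview covers. The dropout call is already planned, and as described it does not take the chance to ask about events since the last interview.

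What is at stake is completeness of one of the two primary outcomes, over five years, in a population whose crises and admissions the Background section itself stresses. Under Evaluation of effect the plan has separate regressions at each time point and a repeated-measures ANOVA over all eleven. Neither, as described, recovers events from an interval that was never asked about.

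**Working it through.** **Inputs.** Look-back 6 months (Primary outcome measures). Visits at months 6, 12, 18, 24, then every 6 months to 60 (Design, Table 1). BPDSI recall 3 months (Primary outcome measures). Cost interview recall 6 months (Cost interview), given at T0 to T4 only (Table 1). Sample size 212 (Sample size). The article gives no missed-visit, dropout or event rate, so it has no figure of its own on this point to reproduce. The sample size is not affected.

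**Rule.** Read literally, an interview held at month v covers months v − 6 to v. The table counts the months of the first 24 that are covered by no interview or by two. The visit timings are illustrative.

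| Interviews held at month | Covered by none | Covered twice |
|---|---|---|
| 6, 12, 18, 24 (on time) | 0 | 0 |
| 6, 18, 24 (T2 missed) | 6 (months 6–12) | 0 |
| 6, 13, 18, 24 (T2 one month late) | 1 (6–7) | 1 (12–13) |
| 6, 14, 18, 24 (T2 two months late) | 2 (6–8) | 2 (12–14) |
| 6, 11, 18, 24 (T2 one month early) | 1 (11–12) | 1 (5–6) |
| 6 only (nothing after T1) | 18 (6–24) | 0 |

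In general, a visit k months late (k up to 6) leaves the first k months of its interval uncovered. If the next visit is on time, the k months after the missed due date fall in two look-backs. These are two different stretches of equal length. A skipped visit causes loss only; overlap needs two interviews less than six months apart.

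One missed visit is 6/24 = 25% of the two-year period, or 6/60 = 10% of five years.

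**Do other instruments cover the gap?** Take T2 missed and T3 on time.
- The BPDSI at T3 reaches back only to month 15, so it says nothing about months 6–12.
- The cost interview at T3 records hospitalizations but reaches back only to month 12. After T4 it is not given at all.
- The dropout interview, as described, has no event questions.

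**Effect of anchoring.** If each interview covers the time since the last completed one, every row in which a later interview takes place becomes 0 and 0. The last row does not change, because time after a patient's final interview stays unobserved unless another contact, such as the dropout call, asks about it.

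**Scale, by assumption only.** If 10–20% of patients missed a given visit, then 0.10 × 212 ≈ 21 to 0.20 × 212 ≈ 42 patients would have no value for that interval. Nothing in the article supports a particular rate in that range.

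**The case against.** The strongest reply is that a six-month recall on a six-month timetable is coherent. With visits on time nothing is lost or overlapped. Visit windows and catch-up rules are commonly left to a full protocol, which is not shown, and central research assistants supervise the timing of assessments (Assessments and clinical outcome measures). A fixed window also gives each patient the same exposure at each visit, including baseline, which suits the planned per-visit regressions. All of this stands. It limits the point to what follows if the stated window is applied literally. It does not remove the point, because the look-back, the timetable and the content of the dropout call are all stated in the article, and no other described source fills the gap.

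A reader might infer more than the article supports:

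- **That events will be lost or double-counted.** This happens only with missed or off-schedule visits and an unextended window.
- **That overlap inflates an event total.** No cumulative count is planned. Overlapping months enter two separate visit values.
- **That dropouts leave outcome assessment.** The paragraph concerns treatment retention, and the article does not say that outcome visits stop when treatment stops.
- **That the loss biases the comparison between arms.** Scheduled therapy contact differs: TAU has one session a month and phase 2 groups meet once or twice a week, although STP-BPD phase 1 is also monthly for each type of session. But outcomes are collected by research assistants, not in therapy sessions. Differential loss is possible, but neither it nor its direction can be derived. That intervals with events are more often missed is plausible but equally undocumented.
- **That the treating hospital's records would close the gap.** Under Treatment as usual, patients in crisis go if necessary to whichever hospital is on duty, while STP-BPD patients go to their own hospital's emergency department. A check limited to the treating hospital could miss TAU admissions and introduce a difference between arms.

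**Conclusion.** The point holds in conditional form. The look-back equals the visit interval, and the dropout interview is described without event questions. If the window is kept at six months whatever the visit timing, each missed visit leaves 6 months of a primary event outcome unasked. Each visit k months late leaves k months unobserved, with k other months entering two visit values when the next visit is on time. The BPDSI and the cost interview do not repair this.

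The size per missed or late visit is exact. The total loss, and whether it differs between arms, cannot be stated from the article. The conclusion assumes that the full protocol has no rule extending the look-back. If it has one, what remains is to say so in the article and to cover events in the dropout call. This is a cheap improvement in data collection, not evidence that the primary comparison is biased.

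**What to change.** 1. Keep the six-month window at T0, where there is no earlier interview.
2. At each later interview, ask about the whole time since the last completed one. Record a date, or at least a month, for each suicide attempt, life-threatening self-harm act and psychiatric admission.
3. Assign each event to its scheduled six-month interval. The planned per-visit analysis then keeps equal exposure, and a missed interval can be filled from the next interview.
4. Add the same event questions to the dropout call already planned.
5. State that patients who leave treatment stay on the T1–T10 schedule for this inventory.
6. Report the count from the fixed six months before each interview as a sensitivity analysis; it can be derived from the dated events.

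Do not rely on a records check limited to the treating hospital.

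The cost is a wording change, a date field and a few questions in an existing call. The downside is less exact recall beyond six months, and step 6 shows how much the results depend on it. Patients who decline the call and never return remain unobserved after their last interview.
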